### Intervention

#### The More and Less program

The ML program is based on the Keeping Foster and Kin Parents Supported and Trained (KEEP) parenting program, which has been tested in multiple settings [36–39]. KEEP is based on Bandura’s Social Learning Theory [40] and Patterson’s Social Interaction Learning Theory [41, 42]. The key concept of the programs is to support parents in evidence-based parenting practices, especially regarding positive reinforcement and limit setting, in order to improve parent and child communication. In ML, the improved communication lays the foundation for parents to support a healthy lifestyle for the child.

The ML program is comprised of 10 weekly sessions (1.5 h/week) and is culturally adapted for Romanian, Spanish, and Swedish families with preschool aged children with overweight or obesity. Table 1 displays the content of the ML program [7, 30]. Beyond the evidence-based parenting practices, the program includes content regarding healthy food habits, physical activity habits, as well as techniques to help parents regulate emotional control. Each session begins with a theoretical introduction to a parenting skill, the focus of the session is then discussed and practice is done through role play and homework assignments. To facilitate the implementation of the ML program it follows a manual where the sessions are described with precise instructions to the group leaders (2 per group). The parents receive a manual which summarizes what has been discussed during each session. For parents who are unable to attend sessions, the parental manual is sent home to the family and the family is contacted by phone for a brief review of the session. To facilitate session attendance the time and location for the groups are planned to suit the parents. Child care is also provided during the sessions.

**Table 1 Tab1:** Session content of the More and Less program and themes included in the MINISTOP app

*More and Less Parenting Program*	
Session	Content
1	Welcome and overview
2	Food and play: When more? When less?
3	Parents as teachers: cooperation and energy balance
4	Parents as teachers: to teach children new behaviors
5	Rewards and incentives
6	Pre-teaching
7	Parents as teachers: limit setting strategies
8	Power struggles: to avoid and to handle them
9	More support – Less stress
10	Summary: parenting, food and play – to prepare for the future
*MINISTOP app*	
Theme	Content
1	Healthy foods in general
2	Breakfast
3	Healthy small meals

#### The MINISTOP app

The MINISTOP app was developed and evaluated in a population based study with preschool aged children (PI: [name]) and has been previously described in detail [17, 18]. Briefly, MINISTOP comprises of an extensive program of information and push notifications built using current guidelines for a healthy diet and physical activity in pre-school aged children [43]. Over the 6-month period 12 themes will be covered (Table 1). A new theme is introduced bi-weekly, with parents being alerted by a push notification when this happens. Every theme is split into three parts (general information; advice; and strategies to change unwanted behavior). Through the app, parents have the ability to register their child’s consumption of sugar sweetened beverages, candy, fruits and vegetables, and physical activity and sedentary behavior. Parents then receive feedback on the registered parameters at the end of every week. Reminder messages are sent out to parents if they have not been in the app after a couple of days [17].

Two days before the tenth and final session of the ML program, parents receive an email with a username and password for the MINISTOP app as well as a text message with a link to download the app. At the final session, the ML program leaders will ensure that all parents were able to download the app and sign in. Thereafter, they will explain how the app works to the parents and answer any questions that they may have.

### Control

The weight management offered to the control group follows the standard care procedure for each country of participation. In Romania and Spain, the control group receives an evaluation of a one-day food frequency questionnaire as well as a 30-min consultation with a doctor that is a specialist in childhood nutrition, where healthy lifestyle recommendations are made. The parents also receive a hand-out which provides general recommendations for healthy food and physical activity in 2 to 6 year olds. Furthermore, in Romania the children are re-evaluated after 3 months during a 15-min consultation. In Sweden, the control group receives standard care according to the Action plan for overweight and obesity for Stockholm County [44]. Children with overweight and children with obesity younger than 4 years receive support from their child health care nurse. Children older than for 4 years with obesity are followed in an outpatient pediatric clinic with yearly visits to a pediatrician and follow-up visits to a pediatric nurse, approximately 5 visits (30 min in duration) per year [7]. The treatment centers around supporting the family in creating healthy diet and physical activity habits for the child. Children may also be referred to dieticians, psychologists or physiotherapists.

### Measures

Outcome measures are collected at baseline, 10 weeks, 9 months, 15 months, and 21 months post baseline. Table 2 presents when outcome measures are assessed and the instruments used to assess child and parental behaviors are displayed in Table 3.

**Table 2 Tab2:** Socio-demographic characteristics and outcome measures collected at different time points

Outcomes	Measure	Baseline	10 weeks	9 months	15 months	21 months
Child						
Weight and height (BMI z-score)	Measured by health care professionals	x	x	x	x	x
Waist circumference		x	x	x	x	x
Date of birth	Child background questionnaire	x				
Country of birth		x				
Sex		x				
Health status		x		x	x	x
Family structure		x		x	x	x
Daycare		x		x	x	x
Visits to health care regarding weight		x		x	x	x
Screen time		x		x	x	x
Breakfast consumption		x		x	x	x
Sugar sweetened drinks consumption		x		x	x	x
Eating behavior	Child Eating Behavior Questionnaire	x		x	x	x
Physical activity / sedentary behavior	ActiGraph wGT3x-BT accelerometer	x		x		
Food intake	Urine samples, 24 h dietary recall	x		x		
Gut hormones	Fasting blood samples	x		x		
Epigenetic markers	Fasting blood samples	x		x		
Parent						
Weight and height (BMI)	Parent background questionnaire	x		x	x	x
Date of birth		x				
Country of birth		x				
Sex		x				
Education level		x				
Health status		x		x	x	x
Occupation status		x		x	x	x
Income		x		x	x	x
Social and economic support from network		x		x	x	x
Perceived level of comfortable life		x		x	x	x
Parenting behavior	Comprehensive Feeding Practices Questionnaire	x		x	x	x

Abbreviations: *BMI* body mass index

**Table 3 Tab3:** Measures used in the study

Instrument, reference	Domains	No. items	Description
Child Eating Behavior Questionnaire (CEBQ),		35	
Wardle et al. 2001 [45]	*Food approach*		
	Food responsiveness	5	The child’s general appetite
	Enjoyment of food	4	The child’s interest in food
	Emotional overeating	4	If the child eats as a response to emotions
	Desire to drink	3	The child’s desire to drink
	*Food avoidance*		
	Satiety responsiveness	5	If the child gets full easily or not
	Slowness in eating	4	The child’s speed of eating
	Emotional undereating	4	If the child eats less in response to emotions
	Fussiness	6	The child eats a limited variety of food
Comprehensive Feeding Practices Questionnaire (CFPQ),		49	
Musher-Eizenman & Holub 2007 [46]	Monitoring	4	Parents keep track of child’s intake of less healthy foods
	Emotional regulation	3	Parents use food to regulate the child’s emotional stress
	Food as a reward	3	Parents use food as a reward for child behaviour
	Child control	5	Parents allow the child control of his/her eating behaviors and parent-child feeding interactions
	Modeling	4	Parents actively demonstrate healthy eating for the child
	Restriction for weight	8	Parents control the child’s food intake with the purpose of decreasing or maintaining the child’s weight
	Restriction for health	4	Parents control the child’s food intake with the purpose of limiting less healthy foods and sweets
	Teaching nutrition	3	Parents use explicit didactic techniques to encourage the consumption of healthy foods
	Encourage balance and variety	4	Parents promote well-balanced food intake, including the consumption of varied foods and healthy food choices
	Pressure to eat	4	Parents pressure the child to consume more food at meals
	Healthy environment	4	Parents make healthy foods available in the home
	Involvement	3	Parent’s encourage child’s involvement in meal planning and preparation

#### Primary outcome

BMI z-score is the primary outcome measure which is the most commonly used indicator of weight change in pediatric obesity studies [47]. The children’s weight and height will be measured to the nearest 0.1 kg and 0.1 cm, respectively. A fixed stadiometer is used to assess height and weight will be measured with the children wearing only underwear. BMI is derived as weight (kg) divided by height (m) squared. BMI z-scores are then calculated using age and gender specific reference values [34].

#### Secondary outcomes

##### Waist circumference

Waist circumference is measured at the mid-point between the lower rib and iliac crest to the nearest 0.1 cm using a non-elastic tape measurer.

Weight, height and waist circumference are measured three times and mean values are then calculated. All children are measured in a standardized manner by trained health care professionals using calibrated instruments.

##### Eating behavior

The children’s eating behavior is assessed using the Child Eating Behavior Questionnaire (CEBQ) [45]. It includes 35 items on eating styles comprising eight factors related to the risk of obesity. Parents rate each behavior on a five-point Likert scale (`never´, `rarely´, `sometimes´, `mostly´, and `always´ for items 1 to 13 and `disagree´, `slightly disagree´, `neutral´, `slightly agree´, and `agree´ for items 14 to 49). Mean scores for each sub-scale are calculated. This questionnaire has been found to have high internal reliability and good validity [45, 48–53].

##### Parenting behavior

The Comprehensive Feeding Practices Questionnaire (CFPQ) is used to measure parenting behavior [46]. The CFPQ is a parent-report instrument, designed to measure feeding practices of parents of children aged 2–8 years. It contains 49 items comprising 12 factors, where parents rate each behavior on a five-point Likert scale (`never´, `rarely´, `sometimes´, `mostly´, and `always´). The CFPQ has previously been validated in Brazilian preschoolers [54].

##### Physical activity and sedentary behavior

The ActiGraph wGT3x-BT accelerometer (ActiGraph Corp, Pensacola, USA, www.actiGraphcorp.com) is used to assess physical activity and sedentary behavior over seven consecutive 24 h periods. The ActiGraph will be attached the child’s non-dominant wrist and be worn at all times, except for water-based activities (e.g., showering/bathing or swimming). The recorded movements will be used to estimate time in various activity levels based on appropriate cut-points.

##### Metabolites of food intake

First void urinary samples will be collected from the children and will be used to assess metabolites of food intake. Two urine samples from the child will be collected by the parents at home six and 3 days before the visit to the research group. The third urine sample is collected on the morning of the visit to the research group. The urine metabolite analysis will be carried out as previously described [29]. In brief, urine samples will be measured by proton nuclear magnetic resonance (^1^H-NMR) spectroscopy. Global urinary ^1^H-NMR profiles will be used to predict the quality of the diet using the World Health Organization guidelines as a reference. Individual urinary metabolites associated with the intake of foods will be used to assess the dietary profile of the child. The Dietary Metabotype Score that embodies concentrations of urinary metabolites related to food components and adherence to diet will be developed and validated against one 24-h dietary recall with a parent. The 24-h recall will cover the day before the visit to the research group. For children attending preschool a food diary for teachers to fill out will be collected to cover the food intake not provided by the parent.

##### Epigenetic markers and gut hormones

Fasting blood samples are collected to assess reversibility of metabolic markers through epigenetic markers and the role of gut hormones.

Epigenetic markers

The epigenetic analysis is carried out in white blood cells, which require DNA extraction, bisulphite transformation, and analysis with Polymerase chain reactions (PCRs) or other technologies involving hypothesis driven methylation (CpGs). The unit of measurement/criteria is changes in percentage CpGs. The methodology has been explained in detail elsewhere [55, 56]. Methylation levels will be analyzed following standardized epigenetic methods after bisulphite conversion as described previously [55, 56] in hypothesis- driven specific CpGs.

Gut hormones

PYY concentrations will be measured using an in-house radioimmunoassay (RIA). The assays are highly sensitive and do not cross-react with other gut hormones. Separation of the antibody-antigen complexes from the free antigen is achieved by secondary antibody. The reported intra- and inter-assay variation is 5.8 and 9.8% respectively.

GLP-1 concentrations will be measured using an in-house RIA. This assay is highly specific and sensitive with the antibody cross reacting with 100% of all amidated forms of GLP-1. The assay does not cross react with glycine extended forms (GLP1–37 and GLP9–37) or any other gut hormones. The lowest level of GLP-1 that can be detected by this assay is 7.5 pmol/l. Separation of the antibody-antigen complexes from the free antigen is achieved by charcoal adsorption. The reported in-house intra- and inter-assay variation is 5.4 and 11.5% respectively.

##### Feasibility, attrition, and acceptability

Using semi-structured interviews, the facilitators and barriers of recruitment as well as attrition to the intervention (first 10 weeks, i.e., the ML parent program) and feasibility and acceptability of the MINISTOP app and of the standard care offered are assessed. Both parents and healthcare professionals are interviewed by trained research staff. During the interviews a set of questions are asked to all participants follow-up questions are however based on individual responses. The questions have been tested in pilot interviews with both parents and health care professionals. The interviews are recorded and fully transcribed. Interviews will be conducted before and after the intervention.

##### Sociodemographic data

At baseline parents are asked to fill out a background questionnaire for the child and themselves. Questions for the parent include: health status, sociodemographic factors and social support. For the child, questions include: country of birth, health status, family structure and lifestyle related questions such as food and screen time behaviors.

#### Adverse events

Adverse events will be monitored, reported and handled appropriately. The risks imposed by this research project are deemed to be low, i.e., the burden of the experiments for the research subjects is limited. It is important to note that blood samples collected in the study are optional and not a criteria for participation. However, blood samples are taken by experienced nurses and a pain reducing cream is used to reduce any discomfort. Urinary samples are none invasive and thus cause no risk to the participants. In addition, the investigators have extensive experience conducting behavioral weight control studies, and active efforts will be taken by the research staff to ensure the participating families’ safety. Other adverse events may include psychosocial burden that parents may experience when made aware about their child’s weight status and the sense of guilt that may arise. To handle that, already in the first session of the ML program causes and consequences are reviewed in a non-judgmental way. Also, potential impact on the child’s self-esteem and the way to talk about body weight and obesity with children, if necessary, are addressed.

### Data management

All collected data will be handled as approved by the ethical boards to protect confidentiality. Data is de-identified and entered manually into a database by research staff at the participating site where the data originated from. An identical database is used at each site. To ensure data quality and validity the researchers follow standard operation procedure protocols when entering data. The entered data will be double checked by the person entering the data and random checks will be performed regularly to ensure data validity. The database will be password protected and access is restricted to researchers with passwords. Original data forms will be stored in a secure place at each study site.

### Statistical analysis

Intention-to-treat analysis using generalized linear mixed models with repeated measures will be used to examine the effects of the intervention on primary (aim 1) and secondary outcomes (aim 2) for the total study population (i.e., all three sites). The link function for the primary outcome (BMI z-score) will be the identity and the Gaussian family (equivalent to a linear regression). In secondary outcomes we will use a Gaussian identity and family link function for waist circumference, physical activity and sedentary behavior, and a logarithmic link and Poisson family function (equivalent to a Poisson regression) for child eating behavior and parental feeding practices. A random effect for country will be used to account for the clustered study design. In the models, we will control for relevant covariates such as sex, age, parental weight status, education level, income and foreign background. Random intercept and a random slope for time will be included in the model to control those non-observed confounders specific to each child that could be constant or vary in time, respectively. Furthermore, interactions between variables will be estimated. If missing values in the outcomes (primary and secondary) are more than 10%, these will be imputed through a two-part model (also known as a model for semi continuous data). In this model, we would simultaneously estimate the probability of not being missing (first part) and the outcome (second part), using a mixed generalized linear model, in which we would include, as explanatory variables: age, sex, parental weight status, foreign background, educational level, and the random effects which are aforementioned.

Statistical tests and analyses of the interaction of phenotypical outcomes with epigenetics will include Manhattan plots, volcano plots, principal component analysis (PCA)/cluster, heatmaps, partial least square-discriminant analysis (PLS-DA), correlations and association studies, linear regression models, receiver operating characteristic (ROC) curves and these will be implemented as appropriate.

The means and medians for the gut hormone values before and after the intervention will be compared, using Student’s t test and Mann-Whitney U test, respectively. The differences will be adjusted in a generalized linear mixed model, with an identity link and Gaussian family, including the confounders, both observed and unobserved, indicated above.

For the validation of child food intake with metabolic markers in urine, the urinary dietary model will be derived using previously described methodology [29]. Comparison between the study groups will be carried out using PCA and Monte Carlo cross-validated partial least square-discriminant analysis (MCCV-PLS-DA) methodology. The relationship between dietary biomarkers and the dietary metabolite profile will be carried out using a generalized linear mixed model, with an identity link and Gaussian family, including, again, the confounders.

The semi-structured interviews with parents and health care professional will be fully transcribed verbatim and analyzed using thematic analysis [57].

For our analyses we will use R [35], STATA version 12.1 (StataCorp 2011, College Station, TX, USA) and SPSS Statistics (IBM, Armonk, NY, USA).

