### Participants, eligibility, and recruitment

In total, we aim to include 300 families (*n* = 100 in Romania, Spain, and Sweden, respectively). To be included in this study: children must be between 2 and 6 years old and have overweight or obesity as classified by international cut-offs [34]; have no other underlying medical condition(s); the child has not started any treatment for overweight or obesity; and at least one parent has to have the ability to communicate in Romanian, Spanish, or Swedish depending on the country of participation. Parents who do not own a smartphone compatible with the MINISTOP app will be excluded from this study (i.e., version 10.0 or higher for iOS or version 5.0 or higher for Android).

Recruitment will follow a standardized protocol for all countries. In Romania, family physicians and pediatricians will be involved to hand out information regarding the study to families with 2- to 6-year-olds with overweight or obesity. Parents who want to learn more about the study are provided with a phone number, email address, web page and Facebook page with information of how to contact the research group. Participants will also be recruited, as self-referrals, using an official page for the study on Facebook to be shared with specialized groups.

In Spain, families with children who attend weight and height assessments at their pediatricians at primary care health centers and hospitals will be asked to participate in the study. If the parents are interested in participating, the pediatrician will schedule a visit within a maximum of 7 days to provide them with more detailed information regarding the study and for them to sign the informed consent.

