### Randomization and blinding

After the consent form has been signed, the participants are randomly allocated to either the intervention group (parent support program and mHealth booster) or the control group (standard care as per country) at a 1:1 ratio via a random allocation sequence list (in blocks of three). The sequence list was generated using free software environment for statistical computing and graphics R (version 3.5.1) [35]. The random allocation sequence is managed by a person who has no relationship with recruitment or treatment and opaque envelopes are used to ensure concealment. Those assessing the outcomes are blinded to the treatment allocation; however, owing to the nature of the intervention participants are not blind to their allocation.

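### Poisson regression is prescribed for CEBQ sub-scales scored as means of five-point items (and for CFPQ factors with unstated scoring); its variance assumption does not fit such scores

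*Protocol article*

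**What the plan says.** The Statistical analysis section of the protocol article plans repeated-measures generalized linear mixed models. BMI z-score, waist circumference, physical activity and sedentary behavior get a Gaussian family with identity link. The two questionnaire outcomes instead get "a logarithmic link and Poisson family function (equivalent to a Poisson regression) for child eating behavior and parental feeding practices". Random effects are a country effect plus a child-level intercept and slope for time. No dispersion parameter, quasi-likelihood or robust variance is mentioned.

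The Eating behavior section says of the CEBQ: "It includes 35 items on eating styles comprising eight factors related to the risk of obesity". Responses are on a five-point scale, and "Mean scores for each sub-scale are calculated".

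The Parenting behavior section says of the CFPQ: "It contains 49 items comprising 12 factors, where parents rate each behavior on a five-point Likert scale". It does not say whether the items of a factor are averaged or summed.

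Table 3 lists 3 to 6 items per CEBQ sub-scale and 3 to 8 per CFPQ factor.

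**The concern.** Poisson regression is a model for counts. A mean of a few Likert items is bounded, usually not an integer, and counts nothing. The practical problem is the variance, which the Poisson family sets equal to the mean. If the real variance is much smaller, model-based standard errors are too large and the tests reject far too rarely.

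Improved eating and feeding behaviors belong to the central hypothesis (Hypotheses section) and to the second specific aim. A true change of modest size in a CEBQ sub-scale could be reported as no effect because of the chosen family, not because of the data.

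**Working it through.** **No figure to reproduce.** The protocol states no mean, SD, effect size or power for any sub-scale. Its only sample-size figure (75 per group, 0.3 BMI z-score, 85% power) concerns the primary outcome and has no bearing here.

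**Inputs.**
- From the documents: "In total, we aim to include 300 families", allocated 1:1, so n = 150 per arm. All three sites are pooled.
- Assumed: items coded 1 to 5, sub-scale mean m = 3, SD s = 0.7, two-sided 5% test, no drop-out, one follow-up comparison. Range examined: m from 2 to 4, s from 0.5 to 1.0.

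**Step 1: does the Poisson variance fit?** A score on 1 to 5 with mean m has variance at most (5 − m)(m − 1). At m = 3 this cap is 4, reached only if half the families answer all 1s and half all 5s. Poisson requires variance 3 (SD 1.73), against 0.7² = 0.49 under the assumption. At m = 4 the cap is 1 × 3 = 3, below the 4 that Poisson requires.

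**Step 2: inflation of the standard error.** For the log ratio of two means, the Poisson model-based variance is 2/(nm) and the true variance is 2s²/(nm²). The ratio of standard errors is therefore R = √m / s.
- m = 3, s = 0.7: R = 1.732/0.7 = 2.47.
- Smallest in range: √2/1.0 = 1.41. Largest: √4/0.5 = 4.00.

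**Step 3: power.** For an effect of d SDs, λ = d√(n/2) = 8.66d. Gaussian power is Φ(λ − 1.96). Model-based Poisson power is Φ(λ − 1.96R), where 1.96 × 2.47 = 4.85.

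| d | λ | Gaussian | Poisson, m = 3, s = 0.7 | Poisson over the range |
|---|---|---|---|---|
| 0.3 | 2.60 | 74% | 1.2% | 0% to 43% |
| 0.5 | 4.33 | 99% | 30% | 0% to 94% |
| 0.8 | 6.93 | >99% | 98% | 18% to >99% |

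The type I error at m = 3, s = 0.7 is about 0.000001 instead of 0.05. With 120 per arm (20% loss, assumed), the first two comparisons become 0.6% against 64% and 16% against 97%.

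**Step 4: simulation.** Five-point items were averaged over 3, 5 or 8 items, with 150 per arm and 600 runs per setting. Mean was 3 and SD 0.68 to 0.78. R came out at 2.2 to 2.6. Model-based Poisson rejected in 0.3% to 0.8% of runs at 0.3 SD and 19% to 24% at 0.5 SD, against 55% to 70% and 96% to 99% for linear regression. Poisson with robust standard errors matched linear regression closely, including under no effect.

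**Step 5: the random effects.** In a log-link Poisson model with a normal random effect of variance τ², the marginal variance is μ + μ²(exp(τ²) − 1), where μ is the marginal mean. This is never below μ, so random effects cannot absorb under-dispersion. If their variance is estimated at zero, the model also loses the gain from repeated measures. For a baseline-to-follow-up contrast with within-child correlation 0.5 (assumed), R becomes 2.47/√0.5 = 3.5.

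**Step 6: if CFPQ items are summed.** For k items the sum has mean 3k and SD 0.7k, so R = √(3k)/(0.7k) = 2.47/√k. This gives 1.43 (3 items), 1.24 (4), 1.11 (5) and 0.87 (8). For the 8-item factor the standard error would be too small.

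**The case against.** Several stronger statements are tempting, and the documents do not support them.

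- **That all 20 sub-scales lose nearly all power.** Mean scoring is documented only for the 8 CEBQ sub-scales. For the 12 CFPQ factors it would be an inference. Under sum scoring the inflation is modest for most factors and reversed for the longest.
- **That standard errors are 2.5 times too large as a fact of the plan.** The figure needs an assumed mean and SD, and the defensible range is wide. A variance near 0.5 is plausible for such averages but is not a bound.
- **That power is lost whatever the effect.** At 0.8 SD the single-visit loss under the central assumption is about two percentage points.
- **That the results would be uninterpretable.** A log link gives a ratio of means. It is awkward, because it depends on the coding: a 0.3-point shift is 3.3/3.0 = 1.10 on 1 to 5 coding but 2.3/2.0 = 1.15 on 0 to 4. It can still be read.

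The best defence is that an article names the family and link and may leave the variance estimator to an analysis plan not seen here. Robust standard errors would largely remove the problem, so the harm is conditional on model-based ones. That condition stands. The choice of family, however, is stated in the article, and it does not fit the scoring the article gives for the CEBQ. The error for mean scores is also conservative, so it would not create a false claim of benefit.

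**Conclusion.** The point holds in limited form. For the CEBQ, the prescribed count model conflicts with the mean scoring in the same article, and the planned random effects do not repair it. For the CFPQ, the scoring is unstated: the Poisson variance would be too large under item means, and under sums too large for short factors and too small for the 8-item one.

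The size is conditional on assumed values and on model-based standard errors. With mean 3, SD 0.7 and 150 per arm, small effects would almost never be detected, moderate ones in under a third of trials, and large ones nearly always. The primary outcome is analysed with a Gaussian model and is untouched. This should be corrected before analysis, but it does not threaten the trial's main conclusion.

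**What to change.** In the Statistical analysis section, move child eating behavior and parental feeding practices into the Gaussian identity-link mixed model already specified for waist circumference, physical activity and sedentary behavior, and report differences in points. In the Parenting behavior section, state that CFPQ factors are scored as item means. If a log-link model is kept, specify robust standard errors.

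The cost is one sentence in each section. Data collection, sample size and trial conduct do not change.
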